**Figure 1 figure1:**
[figure not shown]
Structural equation model to test stigma and gender affirmation as mediators of relationships between service delivery type and HIV outcomes.

### Exploratory Analyses for Aims 1 and 2

We will conduct 3 exploratory analyses. First, using longitudinal data from baseline, 3, 6, 9 and 12 months, we will perform mixed-effects regression modeling to analyze changes in stigma scores, psychological gender affirmation scores, and GAHT use over time by service delivery model. Mixed-effects regression is most appropriate for clustered longitudinal data as it captures correlations of repeated measures using random effects that describe cluster-specific trends over time [100]. Second, as sample size allows, we will assess HIV outcomes by subgroups. The D-i-D model, used to test hypothesis 1 and hypothesis 2, will be fit separately for subgroups defined by (a) gender identity, (b) sex assigned at birth, (c) individual care facility, and (d) colocated versus stand-alone TG-DSD sites. Third, the association between 12-month HIV outcomes (viral suppression rates and prevention-effective adherence rates) and implementation metrics from aim 1 will be examined graphically for the 4 TG-DSD sites by plotting the HIV outcomes at each site versus mean scores on the AIM, IAM, and FIM, respectively.

The use of D-i-D analyses implicitly assumes that TG-DSD sites are either comparable with SSD sites (other than the DSD approach) or that we can readily adjust for any differences. However, if we find that groups differ on important characteristics, we will use inverse probability of treatment weighting to adjust for the covariates in the effect estimation to mitigate potential bias.

### Data Analysis for Aim 3

We will use the data from the microcosting exercise as well as existing data on SSD costs to estimate the incremental cost of TG-DSD over SSD from the health care system perspective. Integrating data collected for aim 2, we will then calculate the cost per successful outcome (defined as viral suppression for those participants on ART or prevention-effective adherence for the participants who are HIV negative at month 12) and the cost of producing an additional client with a successful outcome. Finally, using any available size estimates for the overall transgender population in South Africa [5], we will then calculate the total budget required for a national rollout of TG-DSD in South Africa, incremental to the country’s HIV budget on which we will have real-time data.

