	**Client**			
		IDIs with transgender participants	Tell me about your experience receiving care at the site.	
		Survey with transgender participants	Intersectional stigma scale by Scheim and Bauer [77], Psychological Gender Affirmation scale by Sevelius et al [78], and GAHT use by self-report.	
		Laboratory test with transgender participants	HIV RNA level by serum analysis (for transgender participants on ART) and tenofovir level by DBS^i^ (for transgender participants on PrEP)	

^a^GAHT: gender-affirming hormone therapy.

^b^ART: antiretroviral therapy.

^c^PrEP: pre-exposure prophylaxis.

^d^KII: key informant interview.

^e^AIM: Acceptability of Intervention Measure.

^f^IAM: Intervention Appropriateness Measure.

^g^FIM: feasibility of intervention measure.

^h^IDI: in-depth interview.

^i^DBS: dried blood spot.

Qualitative interview (KII and IDI) recordings will be transcribed and translated into English. The transcripts, field notes, and narrative summaries will be uploaded into qualitative data management software, Atlas.ti (ATLAS.ti Scientific Software Development GmbH), to facilitate analyses. During regularly scheduled meetings, the study team will review field notes, transcripts, and summaries; discuss emerging themes; and revise interviewing and coding strategies, as needed.

Statistical analysis of quantitative data will be performed using Stata (StataCorp) and MPlus (Muthén & Muthén). Data exploration of key variables will be conducted to assess for implausible values and determine whether statistical assumptions (eg, normal distributions of data) for planned statistical analyses are satisfied. Categorical variables will be reported as frequencies and percentages, with means and SDs or medians and IQRs reported for continuous variables. Patterns of missing data will be examined, including testing for differences between participants with and without missing data. A series of sensitivity analyses will be conducted to evaluate the robustness of conclusions drawn from the primary models to departures from the missing at random assumption by comparing the magnitude of the primary effect. In the rare situation that >10% missing data is observed, we will use multiple imputation, as appropriate. We will specify 2-sided tests, .05 significance level (α=.05), and compute 95% CIs throughout.

### Qualitative Data Analysis for Aim 1

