### Statistical Power

Power analyses and sample size calculations were based on the primary outcome of viral suppression (aim 2). No viral load data are available for transgender people in South Africa disaggregated from other key populations. The only South African data that includes transgender women and uses the current nationally recommended threshold for viral suppression includes cisgender men who have sex with men. Nonetheless, the study found a viral suppression rate of 47% [101]. One study of transgender people receiving TG-DSD in South Africa found that those on GAHT were 3 times more likely to be virally suppressed compared to transgender people who are not on GAHT [49]. This suggests an effect size of at least 20%. We consider an effect size as low as 15% to be clinically significant.

On the basis of the aforementioned data and clinical experience, we anticipate that current viral suppression rates will be approximately 65% at baseline, rising to 85% at 12 months among TG-DSD participants, and approximately 61% at baseline, rising to 66% at 12 months among SSD participants. This 20% difference from baseline to 12 months for TG-DSD participants and 5% difference from baseline to 12 months for SSD participants represents a difference in the absolute change in viral suppression rates of 15%. Using *r*=1, α=.05, power of 1− β=.80, and p_1_=viral suppression in the SSD and p_2_=viral suppression in the TG-DSD group and difference of p_2_ – p_1_=.15, the minimum sample per group will be 172 for both TG-DSD and SSD, for a total minimum sample size of 344. Adjusting for loss to follow-up of approximately 12%, a sample of ≥200 in each group, for a total of ≥400 transgender people on ART, provides adequate statistical power for planned analyses.

Loss to follow-up is a challenge for any longitudinal study. We will make every effort to minimize loss to follow-up by collecting multiple forms of contact, reaching out monthly to update contacts, collecting data in the field as well as the study site, and providing remuneration for study participation. We are enrolling a larger sample size than required by the power calculations to allow for potential loss to follow-up without loss of statistical power.

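### Exploratory subgroup D-i-D models are fitted separately by gender identity and sex assigned at birth, so the plan gives no estimate or test of whether the TG-DSD effect differs between subgroups (minor)

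*Protocol article*

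**What the plan says.** The section on exploratory analyses for aims 1 and 2 lists subgroup work as the second of three exploratory analyses, to be done only where sample size permits. The D-i-D model used for hypotheses 1 and 2 "will be fit separately for subgroups defined by (a) gender identity, (b) sex assigned at birth", and also by individual facility and by colocated versus stand-alone TG-DSD site.

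The data analysis section for aim 2 defines the D-i-D estimator as the coefficient of time by service delivery model. Age and gender identity enter that model as covariates. No term lets the TG-DSD effect vary with a subgroup, and the article mentions no heterogeneity test.

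The overall approach to data analysis sets the general rule: "We will specify 2-sided tests, .05 significance level". The same sentence asks for 95% CIs throughout.

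The statistical power section plans for "power of 1− β=.80" in the whole ART stratum. The target "represents a difference in the absolute change in viral suppression rates of 15" percentage points.

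**The concern.** A subgroup analysis is usually read to learn whether an effect is the same across groups. That is a question about a difference between effects, and separate fits do not answer it: they give one D-i-D, one interval and, under the general .05 rule, one p value per group. Without a stated contrast, the easiest comparison for a reader is which groups reached significance. That depends heavily on group size, even when the effects are equal.

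This has some weight here. The introduction describes transgender men and nonbinary people as largely overlooked in the HIV response, so results by gender identity may be read closely. The recruitment text stratifies the cohort by HIV status and service model, with a quota for TG-DSD sites, but states no quota by gender identity. Subgroup sizes are therefore uncontrolled and may be unequal. A non-significant result in a small group could be taken as no benefit when it reflects only the number of people in it.

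**Working it through.** **Inputs from the article.** Two-sided α = .05; power .80; target D-i-D 15 percentage points; anticipated suppression "approximately 65% at baseline, rising to 85% at 12 months among TG-DSD participants"; for standard sites, 61% and then 66% at the same two time points; and "the minimum sample per group will be 172 for both TG-DSD and SSD".

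**Assumptions.** The article gives no subgroup sizes, so all splits below are assumed. Subgroups are treated as independent with the same true effect, and site clustering is ignored.

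**Step 1: the plan's own figure.** For two proportions with equal groups and no continuity correction,

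n = [1.960·√(2·p̄·(1−p̄)) + 0.842·√(p₁(1−p₁) + p₂(1−p₂))]² / (p₂−p₁)².

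The article does not state p₁. The cited South African data ("the study found a viral suppression rate of 47" percent) give p₁ = .47, p₂ = .62 and p̄ = .545, so n = (1.380 + 0.586)² / 0.0225 = 171.8, or 172. The stated minimum is reproduced. A few other values of p₁ (.37, .38, .48) also give 172. This is a comparison of two proportions at one time point; step 4 checks how much that matters.

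**Step 2: power within a subgroup.** With 80% power overall, the expected test statistic is 1.960 + 0.842 = 2.802. A subgroup holding share f of the sample has expected statistic 2.802·√f, and its power is

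1 − Φ(1.960 − 2.802√f) + Φ(−1.960 − 2.802√f).

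**Step 3: chance that the subgroups disagree on significance.** For two groups this is P₁(1−P₂) + P₂(1−P₁). For three it is 1 − P(all significant) − P(none significant).

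| Assumed split | Power in each | Chance of mixed results |
|---|---|---|
| 50:50 | 51%, 51% | 50% |
| 70:30 | 65%, 34% | 55% |
| 80:20 | 71%, 24% | 61% |
| Equal thirds | 37% each | 70% |
| 80:10:10 | 71%, 14%, 14% | 77% |

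If the common true effect is zero, the two-group figure is 2 × .05 × .95 = 9.5%.

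**Step 4: sensitivity to the power assumption.** The D-i-D can be computed directly from the four anticipated rates with 172 per group and within-person correlation ρ, which the article does not give. At ρ = 0 the variance is (.2275 + .1275 + .2379 + .2244)/172 = .00475, so the standard error is .0689 and the expected statistic is .15/.0689 = 2.18. Overall power is then 59%. For ρ from 0 to 0.7, overall power runs from 59% to 97%, and the 50:50 chance of mixed results lies between 34% and 50%.

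**Step 5: what an interaction term would give.** Under identical effects its false-difference rate is the nominal 5% per factor. For precision, 80% power at 15 points implies an overall standard error of 15/2.802 = 5.35 points. Each half has 5.35·√2 = 7.57, and the difference between halves has 7.57·√2 = 10.71. A true 15-point difference between equal halves therefore has expected statistic 15/10.71 = 1.40, or about 29% power, and the 95% CI is about ±1.96 × 10.71 = ±21 points.

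**The case against.** The strongest reply has four parts.

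- **Nothing says subgroups will be compared by significance.** This is correct. The article says only that HIV outcomes will be assessed by subgroup. A reader might infer that subgroup effects will be judged by which fits are significant, or that TG-DSD will be declared ineffective in transgender men or nonbinary people. The text supports neither inference.
- **The analysis is exploratory and conditional on numbers.** Also correct, and it lowers the weight of the point. Very small groups may never be fitted. The article gives no threshold for that condition, however, and neither the label nor the condition supplies the missing contrast.
- **Confidence intervals are promised throughout.** They are, so each subgroup will have more than a p value. Because these subgroups contain different people, a reader could approximate the difference from the separate estimates, apart from the shared sites. Separate fits also give much the same subgroup coefficients as a fully interacted model. What the plan lacks is a commitment to report the difference.
- **An article may leave a heterogeneity test to the analysis plan, which is not shown.** That would answer a complaint about missing detail. Here the article names a method, separate fits, so the point concerns a stated choice. An analysis plan could still add the interaction without contradicting it.

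A reader might also take from the 50% figure that subgroups with identical effects will in general look different half the time. That does not follow. The figure needs a true effect near the design effect, two roughly equal groups and judgement by significance.

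**Conclusion.** The point holds as a minor one. For gender identity and sex assigned at birth, the stated method provides an estimate and 95% CI within each subgroup but specifies no estimate or test of whether the TG-DSD effect differs between them. No primary conclusion is affected.

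The 50%, 55% and 61% figures describe a misreading that the plan leaves open; they are not error rates of a procedure it adopts. They rest on 80% overall power, an equal non-zero effect in both subgroups, assumed splits and no allowance for clustering. They fall to 9.5% with no effect, and the equal-halves figure is 34% to 50% under the plan's four rates with an assumed within-person correlation of 0 to 0.7.

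**What to change.** For subgroup factors (a) and (b), replace the separate fits with one model per factor that adds a time by service-model by subgroup term and its lower-order terms. Report the between-subgroup difference in D-i-D with its 95% CI as the result. Show the subgroup-specific D-i-Ds from that same model with their intervals, as description and without separate significance claims. Keep the exploratory label.

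The remedy is limited to (a) and (b). Read literally, factor (c) needs its own rewording, because each facility offers a single service model and a time by service-model term cannot be estimated within one facility.

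The cost is wording only, with no new data or visits. The drawback is low precision: about 29% power for a 15-point difference between equal halves, and less if the groups are unequal. A non-significant interaction must therefore not be reported as evidence that the effects are the same. The width of the interval should be stated as the reason.

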## Methods

### Overall Study Design

Jabula Uzibone is an observational, multisite, mixed methods, and prospective implementation study. To meet the first aim, we will assess the implementation of TG-DSD models and SSD models at the facility level using standardized observation checklists at 8 facilities (1 DSD site and 1 SSD site per area in all 4 areas). We will examine implementation, acceptability, feasibility, and barriers to and facilitators of TG-DSD via key informant interviews (KIIs; n=6 per site) with health facility staff. At the client level, we will conduct in-depth interviews (IDIs) with 30 transgender people (15, 50% from DSD sites and 15, 50% from SSD sites) drawn from the longitudinal cohort enrolled for aim 2 described in the next paragraph.

To meet the second aim, we will enroll a cohort of ≥600 transgender people and follow them for 12 months. Of the transgender people enrolled, ≥400 (66.7%) will be transgender people living with HIV. This will include ≥200 (50%) who receive ART at TG-DSD sites and ≥200 (50%) who receive ART at SSD sites in the same area as the TG-DSD sites. We will also enroll ≥200 transgender people without HIV. This will include ≥100 (50%) participants without HIV at TG-DSD sites and ≥100 (50%) without HIV at SSD sites in the same area as the TG-DSD sites. Each participant will complete a quarterly survey to assess engagement in HIV prevention and care, changes over time in experiences of gender affirmation, and experiences of stigma.

For participants on ART, we will measure HIV RNA levels (ie, viral load) at baseline and 12 months. For participants on PrEP, we will measure tenofovir levels at baseline and 12 months. For participants who are HIV negative and not on PrEP, we will assess self-reported condomless sex. Prevention-effective adherence is defined as being HIV negative and meeting one of the following criteria: (1) adherent to PrEP based on tenofovir levels, (2) self-report of consistent condom use in the prior 30 days, or (3) self-report of no anal or vaginal sex in the prior 30 days. Table 1 presents a list of data collection activities organized by level of analysis, participant type, and month of enrollment.

**Table 1 table1:** Data collection activities by level of analysis, participant type, and month of enrollment.

Level			Participant, n (%)		Baseline		Months 3, 6, and 9		Month 12

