### Study Procedures

#### Facility-Level Eligibility, Recruitment, and Data Collection

We have enrolled all 4 Wits RHI TG-DSD sites listed in Table 2. In collaboration with district health departments, we have recruited 1 SSD site within the catchment area of each DSD site for a total of 4 TG-DSD sites and 4 SSD sites. SSD sites are similar to TG-DSD sites in urbanicity, socioeconomic status of the client population, and types of HIV services offered (ie, both ART and PrEP). We shared information about the study with the district and SSD site leadership and invited them to participate in the study. Study staff will visit all 8 recruited sites (TG-DSD and SSD) to complete a standardized observation checklist at baseline and 12 months. Checklist items include the number, type, and role of staff; content and frequency of staff training; facility hours, amenities (eg, number of rooms), and community outreach efforts; standard policies and procedures for delivery of HIV and sexually transmitted infection testing, PrEP, ART, and GAHT services, including, but not limited to counseling, prescribing, dispensing, laboratory monitoring, tracking, and visit frequency; sex and gender documentation on clinical forms and records; the number of transgender clients; number of transgender people prescribed GAHT; number of transgender people prescribed PrEP; number of transgender people prescribed ART; availability and use of psychosocial services; and cost of service delivery.

Leadership at each recruited site facilitate recruitment of 6 staff members per site (n=48) to complete a KII at baseline and 12 months. Eligible staff members are aged ≥18 years and work for 1 of the TG-DSD sites or a selected SSD site. We enroll 1 person in each role at each site, that is, peer navigator, community liaison officer, social worker, community health worker, nurse, and site manager. If a staff member leaves between baseline and 12 months, we will interview another person in the same role for the 12-month time point. We contact potential key informants via email or WhatsApp and invite them to participate.

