We will use quantitative methods to evaluate the effectiveness of TG-DSD for viral suppression and prevention-effective adherence and to assess stigma and GAHT use as potential mediators. As noted earlier, our first hypothesis is that rates of viral suppression are more likely to increase among transgender people on ART at TG-DSD sites than among transgender people on ART at SSD sites over the 12-month study period.

The primary outcome measure is the proportion of transgender people on ART with viral suppression (HIV RNA <50 copies/mL). Descriptive analyses will summarize HIV viral suppression comparing participants at TG-DSD versus SSD sites as well as by gender identity at baseline and 12 months. Percent distributions will be computed for categorical variables and means, ranges, SDs, medians, and IQRs will be presented for continuous variables stratified by attendance at TG-DSD versus SSD sites. The primary estimate for this aim is the absolute difference in the change in proportion of virally suppressed during the study period between participants at TG-DSD sites and those at SSD sites. A difference-in-difference (D-i-D) analysis will be conducted to account for anticipated differences between groups at baseline (TG-DSD vs SSD). In addition, we will compare differences at 12 months considering baseline values to enhance the robustness of the estimators of the differences in the 2 groups.

A mixed-effects binomial model will be fit, where the binary viral load suppression status of each client is regressed on fixed effects for time (baseline vs 12 months), TG-DSD versus SSD site, the time by site model interaction, and client-level covariates (age and gender identity). In addition, random intercepts for each of the sites will be included in the model to account for within-site correlation. The D-i-D estimator is the estimated regression coefficient for the time by service delivery model interaction term. All models will account for clustering and be adjusted for relevant confounders in baseline covariates.

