The second hypothesis is that rates of prevention-effective adherence are more likely to increase among transgender people who are HIV negative at TG-DSD sites than among those at SSD sites, over the 12-month study period. We will follow the same steps outlined above for the primary hypothesis. However, we define the outcome measure (prevention-effective adherence) as the proportion of (1) participants on PrEP with TFV levels >700 fmol/punch and (2) participants who are not on PrEP who report no condomless intercourse during the prior 30 days. The estimate will be the absolute difference in the change in the proportion who achieve prevention-effective adherence during the study period comparing those at TG-DSD versus SSD sites. In addition, we will estimate the difference between TG-DSD and SSD sites at 12 months, considering baseline values.

Clients who receive SSD services on enrollment may switch to TG-DSD over time, thereby reducing the sample size of the SSD arm and creating a threat to internal validity. To identify and account for switches over time, we will update information about where the participant is receiving care at every study visit. Participants who transfer from an SSD site to a TG-DSD site will be censored after the date of their last visit for the primary analysis. It would be inappropriate and unethical to require participants to continue receiving care at a specific site, therefore we will use careful tracking to inform an exploratory dose-response analysis that considers the amount of time a participant received care at the TG-DSD sites. The amount of time receiving care at the TG-DSD site will be the independent variable, with the change in outcome from baseline to 12 months as the dependent variable.

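### Exploratory subgroup (c) fits the D-i-D model within one care facility, where only one service model exists, so the interaction that defines the estimator cannot be estimated

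*Protocol article*

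**What the plan says.** In the protocol article, Data Analysis for Aim 2, viral suppression is regressed on time, service delivery model, their interaction, age and gender identity. The target is fixed there: "The D-i-D estimator is the estimated regression coefficient for the time by service delivery model interaction term". The same model carries a site effect: "random intercepts for each of the sites will be included in the model to account for within-site correlation". Hypothesis 2 follows the same steps.

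Exploratory Analyses for Aims 1 and 2 then states, subject to sample size, that this D-i-D model "will be fit separately for subgroups defined by (a) gender identity, (b) sex assigned at birth, (c) individual care facility" and, as the last item, "d) colocated versus stand-alone TG-DSD sites". No SSD comparator is named for (c) or (d).

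On facilities, Overall Study Design describes "standardized observation checklists at 8 facilities (1 DSD site and 1 SSD site per area in all 4 areas". Facility-Level Eligibility, Recruitment, and Data Collection confirms the pairing: "we have recruited 1 SSD site within the catchment area of each DSD site".

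**The concern.** A D-i-D contrast needs two service models observed at two times. Subgroup (c), as worded, restricts the data to one facility and therefore to one service model. The model that the plan names for this subgroup cannot produce the quantity that the plan says it produces.

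The stake is limited to exploratory results. If the aliased terms are dropped, what remains is a before-after change with no SSD control, and it should not be read as that facility's TG-DSD effect. At the planned rates, a TG-DSD facility would show a 20-point rise, of which 5 points are also expected under SSD. The planned D-i-D is 15 points.

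**Working it through.** **Inputs from the protocol article**
- 8 facilities in 4 areas, one TG-DSD and one SSD per area (Overall Study Design).
- Fixed effects: time, model, time × model; random intercept per site (Data Analysis for Aim 2).
- Planned viral suppression: TG-DSD 65% to 85%, SSD 61% to 66%; at least 200 per arm on ART; about 12% loss (Statistical Power).

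**Step 1: the plan's target.** (85 − 65) − (66 − 61) = 20 − 5 = 15 points, as the plan states.

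**Step 2: estimability.** Take the design columns [1, time, model, time × model].
- One TG-DSD facility: model = 1 throughout, so model repeats the intercept and time × model repeats time.
- One SSD facility: model = 0 throughout, so model and time × model are both columns of zeros.

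| Data used in the fit | Rank (of 4) | Interaction estimable |
|---|---|---|
| All 8 sites | 4 | yes |
| One TG-DSD facility | 2 | no |
| One SSD facility | 2 | no |
| TG-DSD sites only | 2 | no |
| One TG-DSD site plus one SSD site | 4 | yes |

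So (c) as written gives 8 fits and no D-i-D estimate; by area pair it gives 4 fits and 4 estimates. A site random intercept cannot be identified with one site. In an area pair it coincides with the service-model term, so it has to be left out there too; the interaction remains estimable.

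**Step 3: precision of the area-pair estimate (viral suppression, risk-difference scale).**

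Var = [a + b − 2r√(ab)]/n + [c + d − 2r√(cd)]/n; half-width = 1.96 × √Var, where r is the within-person correlation and
- a = 0.65 × 0.35 = 0.2275
- b = 0.85 × 0.15 = 0.1275
- c = 0.61 × 0.39 = 0.2379
- d = 0.66 × 0.34 = 0.2244

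With equal site shares (an assumption), n = (200/4) × 0.88 = 44 per arm.
- r = 0: Var = 0.8173/44 = 0.01858; SE = 0.136; half-width 26.7 points.
- r = 0.5: √(ab) = 0.1703 and √(cd) = 0.2310, so Var = (0.8173 − 0.4014)/44 = 0.00945; SE = 0.097; half-width 19.1 points.

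| Data | n per arm | Half-width, r = 0 | Half-width, r = 0.5 |
|---|---|---|---|
| One area, equal share | 44 | 26.7 | 19.1 |
| One area, 20% share | 35 | 30.0 | 21.4 |
| One area, 40% share | 70 | 21.2 | 15.1 |
| Two areas, as in (d) with matched SSD sites | 88 | 18.9 | 13.5 |
| All four areas | 176 | 13.4 | 9.5 |

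The 20% floor is the TG-DSD recruitment quota; 40% is the most one site can have if the other three are at the floor (100 − 3 × 20). The paired SSD site is assumed to have the same share, although the quota covers TG-DSD sites only. Power for a 15-point D-i-D in one area at 44 per arm is about 20% (r = 0) to 34% (r = 0.5). All figures ignore clustering.

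**The case against.** The strongest reply is that the intended reading is obvious. With one SSD site per TG-DSD catchment area, a D-i-D by facility would naturally set each TG-DSD site against its area comparator, which is estimable, and a condensed article may leave that detail to a fuller document. This is a fair guess at intent and the reason the point is modest. It does not remove it: the text names a specific model and a specific subgroup, and that combination cannot give the stated estimator.

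Other possible rescues fail:
- The sample-size condition does not help, because the problem is collinearity.
- Switchers do not help. The rule that "Participants who transfer from an SSD site to a TG-DSD site will be censored after the date of their last visit" is limited to the primary analysis, so it cannot be relied on here. But a participant who switches has moved to another facility, and each facility still holds one model.
- Two TG-DSD units stand on SSD campuses, but they are counted as TG-DSD sites and the SSD sites are recruited separately. Even a campus-wide reading would leave the two stand-alone sites without a contrast.

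It also stands that the area-pair estimates are weak. A correlation of 0.5 is near the ceiling for the TG-DSD arm: with 65% and 85%, the maximum is √[(0.65 × 0.15)/(0.35 × 0.85)] = 0.57. So 19 points is close to the best case at equal shares. For hypothesis 2, with 100 per arm planned, one area would have only about (100/4) × 0.88 = 22 per arm.

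A reader might go further in three ways that the document does not support:
- That (d) fails too. It fails only if fitted to TG-DSD sites alone; with SSD sites kept it is estimable.
- That the plan claims to isolate an effect of colocation. It does not.
- That site variation would be lost. The third exploratory analysis plots 12-month outcomes for each TG-DSD site.

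**Conclusion.** The point holds for subgroup (c). As worded, the time by service model interaction is not estimable in any of the 8 facility fits, and only before-after changes can be obtained. This conclusion is structural and rests on no assumed figure. For (d) the gap is narrower: the comparator is not named.

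A reader might infer that the main D-i-D result is compromised. It is not: the pooled model over all 8 sites has full rank, and only exploratory analyses are affected.

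The size of what can be recovered is modest. One area gives a half-width of about 19 to 27 points for viral suppression. That rests on the planned rates (for SSD, "approximately 61% at baseline, rising to 66% at 12 months among SSD participants"), 12% loss, equal site shares, within-person correlation between 0.5 and 0, and no allowance for clustering. With one site per model in each area, the estimate also cannot separate the service model from other changes at that site.

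**What to change.** 1. Define subgroup (c) as the four area pairs: each TG-DSD site with the SSD site in its catchment area.
2. Omit the site random intercept in these fits, because site and service model coincide within a pair.
3. Report the four area estimates with confidence intervals as descriptive only.
4. For (d), state that each TG-DSD group (colocated, stand-alone) is compared with its own area-matched SSD sites.

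The cost is wording. No new data are needed, because the design already has one TG-DSD and one SSD site per area. The drawback is that the four estimates will be imprecise and cannot support claims about any single site.
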